**Secondary Objectives: Clinical Outcomes**

1. Evaluate the effect of EPIC WheelS on wheelchair skill capacity and obtain an estimate of the treatment effect size;
2. Evaluate the effect of EPIC WheelS on wheelchair skill safety, wheelchair confidence, satisfaction with activity performance, mobility, and health-related quality of life.

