**Methods**

**
[figure not shown]
1. Research Design.** This 2-year feasibility study will use a two-site (Winnipeg and Vancouver) randomized controlled trial to compare differences in older adults’ wheelchair mobility skills with EPIC WheelS versus usual care. Subjects will be randomly assigned to the experimental group (usual care + EPIC WheelS) or a control group (usual care only) using a 1:1 allocation ratio between groups. To support balance between groups and masking of assignment, a central computerized randomization process will be designed by our team statistician ([name]), with an undisclosed block size and stratified by site (Winnipeg *n* = 20; Vancouver *n* = 20). Once subjects are enrolled, the Study Tester will collect baseline data and enter them into a secure database. The Site Coordinator will contact [name] via telephone or email and obtain group assignment within 48 hours. Subject contact information will be forwarded to the appropriate group Trainer to arrange for an initial training session or social visit. To address bias, subjects will be instructed not to discuss their program and Study Testers will be blinded to group allocation.

Experimental group subjects will attend 2 training sessions with an expert Trainer. The Trainer will individualize a structured home training program, delivered via a computer tablet, and subjects will train for 1 month. The Trainer will make telephone contact at the end of weeks 1 and 3. Control group subjects will receive 2 social visits to address attention balance through exposure to study personnel. In addition, they will be provided with a similar computer tablet with cognitive training games to account for tablet device and activity exposure.

**2. Assessments.** The clinical outcome measures will be collected at baseline (pre-randomization) and post-intervention. A 1-month intervention will provide ≥ 8 hours of training, which is comparable to clinical studies using the WSTP where a significant improvement in skill capacity was observed.^17-19^

**3. Subjects.** A total of 40 community-dwelling MWC users living in Winnipeg and Vancouver (20 at each site) will be recruited on a volunteer basis (see Section 8.1 for sample size justification). To optimize the impact of the treatment, individuals with less than one year of MWC use will be recruited as they are still developing routines and patterns of wheelchair use and potentially more amenable to adapting their mobility techniques.^12^

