***4.2.2.3 Wheelchair Use Confidence Scale for Manual Wheelchair Users* (WheelCon-M 3.0).** Self-efficacy has been identified as a key component in the performance of wheelchair mobility skills.^47^ EPIC WheelS incorporates principles of Social Cognitive theory, including self-efficacy, to promote program adherence and skill acquisition. Preliminary research has suggested that standardized training can increase wheelchair confidence among older adults.^48^ The WheelCon is a self-report questionnaire composed of 65 statements related to confidence using a wheelchair in activities and environments, each rated on a scale from 0 (“not confident”) to 100 (“completely confident”), producing a total mean score of 0 – 100 (see Appendix K).^49^ A 2010 study identified strong test-retest reliability (ICC = 0.84) and significant correlation with comparison measures supporting its validity.^50^

***4.2.2.4 Life-Space Assessment (LSA).*** The LSA (Appendix L) will capture the mobility habits of study subjects. It is a 20-item questionnaire that tracks the locations to which wheelchair users travel on a continuum of 5 environments from the home to outside of town.^51^ Subjects report on their movement in each life-space during the past 4 weeks, the frequency of travel, and whether assistance was required. Evaluation of the LSA among power wheelchair users found excellent test-retest reliability (ICC = 0.87) with moderate to substantial concordance for 18 of 20 items (*k* = 0.47 - 0.73).^52^

***4.2.2.5 Health Utility Index Mark 3 (HUI3).*** Health utility measurement is useful in performing cost-utility and cost-effectiveness analyses of new rehabilitation interventions. The HUI3 (Appendix M) is a brief questionnaire that asks subjects about their health status, reflected in a single-score measure of *health-related quality of life* (HRQOL)*.*^53^ Test-retest reliability in a study of patients recovering from hip fracture was found to be acceptable for comparing between groups (ICC = 0.72).^54^ Differences of .03 have been found to represent meaningful change.^55^ Our study is not sufficiently powered to undertake a cost-utility analysis, but will determine the feasibility of collecting cost-utility data in a larger RCT and estimate what changes in HRQOL might be anticipated.

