**8. Statistical analyses**

Study analyses will consider study **feasibility** as well as **clinical** (statistical) outcomes. Means and standard deviations (for continuous variables) and frequencies and proportions (for categorical variables) will be used to summarize case mix and outcome variables for groups. Qualitative comparison of variable balance will be made, including determination of prognostic importance.^68^ Descriptive statistics of training time and number of training sessions for the treatment group (collected via tablet usage data) will be used to evaluate dose-response and adherence.

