**8.2 Clinical Outcomes**

***8.2.1 Primary analysis:*** Post-treatment WST skill *capacity* scores will be compared in the experimental and control groups using analysis of covariance (ANCOVA), controlling for baseline score as a covariate.^70^ Borm et al.^71^ demonstrate that correlation between pre- and post-intervention scores (ρ) influences analysis power; when ρ > 0.5, change score is more powerful than direct post-intervention comparison. However, when ρ lies between 0.2 and 0.8, ANCOVA (controlling for baseline score) further reduces the required sample size by 10-40% over change score. Given that preliminary data suggest ρ ~ 0.5,^72^ ANCOVA should provide the most powerful analysis, in addition to reducing error variance and allowing modification when statistical assumptions are not met.^73^ Unequal cell sizes will be accommodated using Method 1 adjustment^74^ and diagnostic assessments made for model assumptions. Significance testing (*p*) and marginal means with 95% confidence intervals will be estimated. Effect size (partial η^2^) will be calculated as a ratio of the effect and total sums of squares, with a 95% confidence interval . To preserve prognostic balance, primary analysis will be based on intention-to-treat; however, since one objective is to estimate the treatment effect, secondary analysis on a per-protocol basis (subjects who adhere to treatment) will also be conducted for comparison.^75^

***8.2.2 Secondary analysis:*** ANCOVA will be used to compare post-treatment scores between the experimental and control groups for WST skill **safety** scores as well as for wheelchair **confidence** (WheelCon) scores and **mobility** (LSA). In each case, baseline score will be used as a covariate. Subjects’ **satisfaction with performance** of meaningful activities (WhOM score) will be analyzed using analysis of variance (ANOVA). Mean administration time for the HUI will be calculated and a preliminary evaluation of change in the treatment group (paired sample *t-test*) will be conducted.

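### HUI3 is tested only for change within the treatment arm, which cannot answer the stated objective on health-related quality of life

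*Combined protocol and SAP*

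**What the plan says.** Secondary objective 2 (Secondary Objectives: Clinical Outcomes) is to "Evaluate the effect of EPIC WheelS on wheelchair skill safety, wheelchair confidence, satisfaction with activity performance, mobility, and health-related quality of life". HUI3 is one of the secondary measures in section 4.2.2. Under Methods, item 2 (Assessments), "The clinical outcome measures will be collected at baseline (pre-randomization) and post-intervention", with no restriction to one arm.

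Section 4.2.2.5 gives HUI3 a narrower purpose. It says the study lacks the power for a cost-utility analysis but will "determine the feasibility of collecting cost-utility data in a larger RCT and estimate what changes in HRQOL might be anticipated". It also states: "Differences of .03 have been found to represent meaningful change".

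Section 8.2.2 opens with "ANCOVA will be used to compare post-treatment scores between the experimental and control groups for WST skill" safety, and applies the same method to WheelCon and LSA, each with its baseline score as covariate. For HUI3 the plan is different: a mean administration time and a "preliminary evaluation of change in the treatment group" by paired t-test. No between-arm test or estimate for HUI3 appears elsewhere. The opening of section 8 says that descriptive statistics "will be used to summarize case mix and outcome variables for groups".

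**The concern.** The objective is about an effect, which in a randomised trial is a difference between arms. The planned HUI3 analysis estimates change over one month in treated subjects only. That change includes whatever would have happened without training. Subjects have used a wheelchair for less than a year and are described as still forming their habits of use, so some change without training is plausible. The background (section 3) cites gains of 3-8% on the WST in control groups. That is a different measure, but it shows that untrained groups move in this field. The control arm's social visits and games tablet were designed to balance attention and device exposure, and the HUI3 test makes no use of them.

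Two things are at stake. A significant paired test could be read as a quality-of-life benefit of training. And the figure carried into the larger RCT, which is meant to address cost-effectiveness, would be a before-after change. Planning that trial needs an incremental difference and its variability.

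**Working it through.** **Inputs from the protocol**
- Meaningful HUI3 difference: 0.03 (section 4.2.2.5).
- Evaluable subjects: 15 per arm; randomised: 20 per arm (section 8.4).
- Alpha 0.10 (section 8.4, set for the WST sample size; no alpha is stated for HUI3).

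**Assumptions**
- SD of HUI3 change: not in the documents. Main values 0.08, 0.10 and 0.15; wider range 0.05 to 0.20.
- Two-sided test.
- A drift of 0.03 common to both arms, with no treatment effect. The protocol gives 0.03 as a meaningful difference, not as an expected drift.
- Baseline-to-post correlation of 0.5 for HUI3, borrowed from the WST value in section 8.2.1.

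**The plan's own figure.** The sample size for the primary outcome reproduces. With a difference of 9.3, SD 9.5, two-sided alpha 0.10 and 90% power, n = 2 × [9.5 × (1.645 + 1.282) / 9.3]² = 17.9 per arm. Multiplying by 1 − 0.5² = 0.75 gives 13.4, so 14, or 15 with one extra subject per group. Then 30 / 0.75 = 40 in total. This fixes the n used below and has no other bearing on the point.

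**Paired t-test under a common drift.** The statistic follows a noncentral t with n − 1 degrees of freedom and noncentrality (0.03 / SD of change) × √n. For n = 15, √15 = 3.873 and the critical value at alpha 0.10 is 1.761.

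| SD of change | Noncentrality, n = 15 | n = 15, alpha 0.10 | n = 20, alpha 0.10 | n = 15, alpha 0.05 |
|---|---|---|---|---|
| 0.08 | 1.45 | 40% | 49% | 27% |
| 0.10 | 1.16 | 30% | 36% | 19% |
| 0.15 | 0.77 | 19% | 22% | 11% |

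Over the wider SD range, 0.20 down to 0.05, the figures for n = 15 are 15% to 71% at alpha 0.10 and 8% to 58% at alpha 0.05.

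**Between-arm ANCOVA on the same scenario.** Data were simulated with 15 or 20 per arm, correlation 0.5, common shifts of 0, 0.3 and 0.5 SD, and no difference between arms. At this correlation the SD of change equals the outcome SD, so 0.3 SD corresponds to the 0.10 row. ANCOVA rejected in 9.6% to 10.1% of trials at alpha 0.10 and in 4.7% to 5.1% at alpha 0.05, whatever the shift. On the same data the paired test with n = 15 and a 0.3 SD shift rejected in 29.8% at alpha 0.10, which matches the table.

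**Precision.** In outcome SD units with n = 15 per arm, the standard error of the ANCOVA difference is √[2 × (1 − 0.25) / 15] = 0.32. That of the one-arm change is √[2 × (1 − 0.5) / 15] = 0.26. The between-arm estimate is somewhat less precise, but it estimates the quantity the objective names.

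**The case against.** The strongest reply is that HUI3 is in this trial mainly for feasibility. The primary objectives list a health utility index as a resource issue, the Hypotheses paragraph leaves quality of life out of the secondary clinical outcomes, and section 4.2.2.5 disclaims power for cost-utility work. Section 8.2.2 calls the analysis preliminary and speaks of change, not of a treatment effect. On this reading the fault lies in the wording of objective 2. That has weight, and rewording the objective would remove the direct contradiction. It would not rescue the other stated purpose, anticipating quality-of-life changes for a larger RCT, because a one-arm change is a weak basis for that.

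Second, the descriptive summaries in section 8 may include control-arm HUI3 means, so the control data are not wholly unused. This is correct, but means and SDs by group give no adjusted difference and no confidence interval, and the only test would still be uncontrolled.

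Third, in the scenario above the treated arm really did change, so the paired test is right about its own hypothesis. Its rejections mislead only if read as an effect of training. This stands, but objective 2 invites that reading. It also stands that the percentages rest on assumed inputs, and that regression to the mean is a minor part of the case, since eligibility does not select on HUI3.

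**Conclusion.** The concern holds. The only HUI3 inference in section 8.2.2 cannot answer secondary objective 2, and it does not supply the between-arm difference needed for planning the RCT. The mismatch is structural and needs no assumed number. The 19% to 40% range (15 completers, two-sided alpha 0.10, common drift 0.03, SD of change 0.15 down to 0.08) only illustrates how often drift alone would produce a significant paired test; it is not a forecast. HUI3 is a secondary, explicitly preliminary measure in a feasibility trial, so the primary WST conclusion is untouched. It should still be corrected, because the repair is nearly free.

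**What to change.** In section 8.2.2, replace the paired t-test with an ANCOVA of post-treatment HUI3 on arm and baseline HUI3. Report the adjusted between-arm difference with its confidence interval, labelled exploratory, together with the residual SD for planning the RCT. Adding site is sound because randomisation is stratified by site, although the other secondary models in section 8.2.2 adjust for baseline only. Keep mean administration time, and give within-arm change for both arms as description without a test.

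If the investigators intend HUI3 for feasibility only, the alternative is to reword secondary objective 2 to say so. They would then also have to drop the claim that the one-arm change shows what a larger trial might expect.

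The cost is a change of wording in the analysis section. Both-arm collection at both times is already implied by the assessment schedule, so no extra subjects, visits or data are needed.

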**8.3 Post-Treatment Qualitative Analysis**

After the feasibility clinical trial is complete, semi-structured interviews will be used to explore subjects’ experience with the EPIC WheelS intervention. The use of qualitative methods in conjunction with RCT studies in rehabilitation has been highly recommended to support construct validity of the quantitative outcome measures, identify additional contextual variables that mediate intervention active ingredients, and uncover unexpected findings.^76, 77^ Exploring the benefits of specific skill acquisition among EPIC WheelS subjects will provide valuable information regarding what a *clinically important difference* is for subjects. A criterion-based purposive sample (i.e., 3 highest and 3 lowest WST change score at each site) will be selected using a maximum variation strategy to provide diverse perspectives representative of the range of subjects.^78, 79^ [name] will conduct all of the individual interviews using a semi-structured question guide focusing on treatment fidelity, the training intervention, and impact on engagement in community-based activities (see Appendix F). [name] has considerable clinical and research experience conducting interviews. [name] and [name] will perform all data analysis using a *directed content analysis* approach where key concepts from existing evidence and study hypotheses form the initial coding categories.^80^ Strategies for ***authenticity and rigor*** will include sampling using treatment outcome, substantive engagement between interviewer and subjects, and documenting an audit trail. Triangulation will be supported through peer debriefing, collaborative theme analysis, member checking, and integration of the quantitative and qualitative findings.^79^ The qualitative findings will be used to enhance and interpret the clinical outcomes, such as key intervention ingredients; relevant outcomes that might not be captured; and explanation for potential conflicting quantitative results. Quantitative and qualitative findings for each subject will be summarized in table, or meta-matrix,^81^ to identify both patterns and paradoxes between the results.^82^

**8.4 Sample size justification*.*** To address the feasibility outcomes, the number of subjects is large enough to represent the target population and assess the feasibility criteria.^69^ In addition, the sample size is powered to detect a statistically significant difference between groups and provide a reasonable estimate of a treatment effect. The sample size calculations are based on the primary *clinical* outcome (WST), as this will be used in subsequent EPIC WheelS studies. Research in the field of wheelchair skills training is still maturing, with 3 published studies using actual users, and given the novel home program approach an ∝ of .10 was selected to ensure a potentially beneficial treatment effect does not go undetected (Type I error rate). To minimize the risk of identifying such an effect merely by chance (Type II error), the study is powered at 90%. Based on a sample size calculation formula for ANCOVA in RCT designs^71, 83^ each group would require 15 subjects (see Appendix Q for details). In previous Canadian trials, a 9-18% dropout rate has been reported; conservatively adjusting for a 25% dropout rate, a total study N of 40 is planned (n = 20 for each group).

Previously published studies have used younger or mixed age populations and data specific to older adults are not available. We obtained permission to use a data subset (adults > 50 years) from a yet-to-be published study^72^ providing WST change scores following training and powered our study to capture a comparable change (*m* = 9.3%; *s* = 9.5%). A difference of 9.3% corresponds to acquisition of 3 additional skills on the WST; previous studies report subjects’ perceptions of a *clinically important difference* with such improvements.^17, 18^ In fact, the skills performed on the WST are sequenced from simple (e.g. rolling forwards) to moderate (e.g., propelling on carpet) to complex (e.g., ascending 10° ramp). Research literature reporting on MWC use among older adults specifically implicates carpet, inclines, curbs, gravel and poor sidewalk conditions as barriers to independent mobility.^7^ Acquisition of **even one of these important skills** could quite reasonably represent a minimally clinically important difference (MCID) to wheelchair users, their caregivers, and those providing training. No formal MCID has been established for the WST; however, using data from a Canadian trial,^18^ a Smallest Detectable Difference calculation suggests a difference of 9.2% would exceed any measurement error or noise.^84^ A Reliability Change Index calculation indicates 3.0% is the Minimal Detectable Change required and is a reasonable proxy for MCID^84^ (details in Appendix Q).

**TIMELINE**

[figure not shown]
The study will be conducted over 2 years, between October 2012 and October 2014. Data collection will occur over 13 months between December 2012 and December 2013, projecting recruitment of 3 subjects per month. Qualitative interviews will then be conducted, followed by analyses and knowledge translation activities.

The two sites selected for the study are Winnipeg and Vancouver. These two locations represent different provincial approaches to wheelchair procurement in Canada and therefore enable us to assess whether disparate approaches to health services will contribute to complications in running a multi-site trial. Manitoba and British Columbia have substantially different wheelchair funding systems, as well as geographic, cultural and climate differences. Both sites have large populations of older adult MWC users, with representatives from both sites previously contributing to the development of the EPIC WheelS program and committed to ongoing input including knowledge translation activities. The study will be conducted at the Blusson ICORD Pavilion and Rehab Research Lab (GF Strong Rehab Hospital) in Vancouver both locations have private rooms for data collection and a separate 600 square foot space housing the WST equipment. The Health Sciences Rehabilitation Centre in Winnipeg is the primary tertiary care centre for the province and has dedicated space for wheelchair training and testing, including the WST equipment.

**2. Recruitment**. There is a substantial and growing pool of older adult MWC users to draw from. The Manitoba Wheelchair Program (MWP), a publicly funded long-term loan program and primary provincial wheelchair provider, identifies nearly ***7200 MWC users over 55*** ***years*** currently in Manitoba. [name] has established connections with clinicians and provincial agencies that provide wheelchair prescription and procurement. British Columbia has a population roughly four times as large and is expected to have at least ***25,000 older adult MWC users***. [name] has developed relationships with therapists who prescribe wheelchairs in the Lower Mainland of Vancouver. For this feasibility trial, we expect to draw on a broad pool of potential subjects through our established relationships with community-based therapists; advocacy and consumer-based groups; recruitment advertising included with delivery of wheelchairs to new users via the MWP; and public advertisement using print, television, and web-based media.

**STUDY Limitations**

Due to the nature of feasibility studies, several inherent limitations arise and will be addressed in the larger multi-site RCT study to follow. The potential for recruitment of *novice* *older adult MWC users* is unknown - this is an important feasibility outcome to address for future planning. Assessment of skill retention will not be addressed. Control group subjects may be more prone to drop-out;^85^ providing social visits, a tablet with cognitive games, and a condensed training DVD at the study conclusion will help mitigate this risk. Demonstration of a treatment effect may lack generalizability due to the restricted age group being targeted. Age is inversely related to motor skill acquisition, including wheelchair mobility skills. We anticipate that a training program proven to be effective with older adults should have at least as large a treatment effect in younger and stronger individuals; however this assumption is as yet untested. The qualitative component uses a restricted sample and is not a comprehensive exploration of subjects’ experience, but will enhance interpretation of the quantitative results and inform any fine-tuning required for the study treatment arm.

